*Experiment B: Does action improve sensitivity to backwards-masked stimuli?* This experiment combines MIB with a type of backward masking of the target stimulus. If the target is backwards-masked to preclude perception in the passive condition—by removing the target as it approaches the foveal region of the visual field—AI-C predicts that the target will still be perceived when the same masking setting is applied in the active condition. If there is no difference between conditions, or if the passive condition results in improved perceptual recognition, this would be evidence against AI-C; otherwise, this will provide evidence that action facilitates conscious awareness, and in that sense will predominantly support the active inference prediction.

Both experiments will also be equipped with measures of autonomic and neuromodulatory (i.e., cardiac and pupil) activity to adjust for any differences in attentional set (e.g., arousal) that could be considered to confound condition-specific differences. Further, in primates, attentional selective sampling under normal conditions is typically associated with motor activity (e.g., ballistic saccades or microsaccades, as well as eye blinks and pupil dilation and constriction), and therefore this study will record not only the saccades in the active condition (for play-back in the passive condition) but also microsaccades, pupil diameter and blinks throughout, in order to quantify differences between two conditions (such as microsaccades when fixating on the relevant location in both the passive and action conditions).

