### Participants, sample size, exclusion/inclusion criteria, and stopping rule

Experiments A and B will be conducted in parallel at the Monash Centre for Consciousness and Contemplative Studies, Monash University (Melbourne, Australia) and the Institute of Psychology, Friedrich Schiller University (Jena, Germany). Identical stimulus materials and programme scripts will be used to run the experiments on identical setups and under very similar circumstances.

Participants will be students and staff recruited through each institution’s internal recruitment system. The general public may also be recruited through email approaches based on flyer responses. Participants in Melbourne will be reimbursed for their time either with course credit or AUD$20-50; participants in Jena will receive a similar rate in Euros or partial course credits. Both research sites have received ethical approval from their respective University Human Research Ethics Committees (Monash Human Research Ethics Committee – Ethics Number: 29238; The Ethics Committee of the Friedrich Schiller University – Ethics Number: FSV 22/093.

Recent MIB work deploying eye-tracking and pupillometry in the MIB paradigm [36] aimed for a target sample size of 55 participants to give a statistical power of at least 80% with an effect size of η2p = .13.; we will adopt this sample size as a stopping point for data collection. Participants must have normal (or corrected-to-normal) vision and audition, and will be aged between 18 and 45 years. Additionally, participants must demonstrate computer literacy and be able to maintain constant fixation for at least 5 seconds in the pre-test period and follow the fixation-based gaze strategy. Respondents will be excluded from participation if they (1) report having previously suffered a stroke or other neurological condition; (2) are currently taking psychoactive medications; or (3) are currently undergoing mental health treatment.

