### Experiment A: Time to reappearance following motion-induced blindness

**Design, stimuli, and procedure.** This experiment deploys a within-subjects design to contrast differences in the time to reappearance of stimuli rendered subjectively invisible by MIB. The MIB task will be performed in conjunction with eye tracking in order to produce both active looking blocks and passive viewing blocks (where the active gaze is precisely replayed).

We will use the Racially Diverse affective expression (RADIATE) face stimulus set [37]. We use only neutral faces for our stimulus set, removing any stimuli with accuracy ratings for neutral emotional state below 80%. This leaves 108 stimulus images of distinct identities (and one used solely for instructional purposes). On each trial, the stimuli will be pseudo-randomly sampled with a constraint that no greater than two consecutive repetitions of a specific identity will be shown to participants. Each target stimulus will be converted to greyscale, scaled to 200x200 pixels, and luminance-matched using the SHINE toolbox [38]. All images will be enclosed in an elliptical mask centred on the face shape. In order to correct the luminance difference created by the mask the luminance of each stimulus image will be scaled to match an RGB value of 100 (+/- 0.1%); the background colour of the display will also be matched to this value.

Target stimuli will be presented at a randomly-selected polar angle (1–360 degrees) 9 degrees of visual angle from central fixation. In each trial, a blue central fixation dot will be present behind the stimulus and a cross pattern filling the entire screen will rotate at 2.7s/cycle, in line with previous work [39]. As the target in this design will either (in the passive case) remain stationary after being moved into central fixation or (in the active case) be foveated by the participant, it will ultimately fill the centre of the visual field in both conditions. This means that central attentional resources will eventually be allocated to it, and it will become visible even in the passive condition. This is consistent with active inference, since attention is a (covert) form of action. However, the thrust of this experiment lies in the role of overt action (eye movement), recognizing that covert attentional resources are also deployed in the passive condition at some point in the task.

Experiment A sessions will be separated into three sections:

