NREP is compatible with motor movement conveying arousing/attentional effects (other than via active inference), which may facilitate early detection. For instance, motor activity can profoundly stimulate V1 firing activity, and motor-associated arousal may help to detect stimuli at greater distance from foveation point. Thus, for Experiment A (see Table 1), NREP predicts either decrease or no change, with medium confidence; for Experiment B (see Table 2), NREP predicts increase or no change, with medium confidence.

In addition to the two main hypotheses, we also predict the following, based on AI-C, which is not part of the adversarial collaboration and thus do not elicit predictions from the competing theories:

3)
*In Experiment B target stimuli will be discriminated more accurately in active vs. passive trials given the same frequency of reappearance.*
4)
*In Experiment B confidence in target discrimination will be higher in active vs. passive trials given the same frequency of reappearance.*

In the setting of the overall adversarial collaboration (TWCF ARC INTREPID), these sets of predictions will be considered in conjunction with predictions from all theories on three main experiments, in total. The aspiration is that this total set of findings from all experiments will strongly distinguish among these three theories (even if individual experiments are not able to strongly distinguish them). Table 3 illustrates some of the main predictions and confidences of each theory for selected, key parameters for each experiment, with Experiment 3 being described in this study protocol (for full details, please see the preregistration).

**Table 3 pone.0328836.t003:** Illustration of predictions and confidences for each theory about each consortium experiment (for selected, key parameters); for the full prediction tables and specification of the parameters, please consult the INTREPID preregistration.

Experiment	IIT	NREP	AI-C
1	Confirm prediction, high confidence	Predict no change, high confidence	Predict no change, medium confidence
2	Confirm prediction, medium confidence	Confirm prediction or predict no change, high confidence	Predict no change, medium confidence
3	Confirm prediction or predict no difference, low confidence	Confirm prediction or predict no difference, medium confidence	Confirm prediction, high confidence

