### Planned analyses and expected outcomes

In order to capture the contribution of covariates within both experiments, 3A and 3B dependent variables will be analysed under a generalized linear modelling framework based on a pre-specified decision tree (see Fig 3). The choice of link-function will be informed by the distributional properties of the data and the evaluation of standard model diagnostics (e.g., Q-Q plot of residuals) and indices of marginal likelihood (e.g., AIC). Nested model comparison will be used to evaluate whether model fit is significantly improved by the inclusion of focal parameters. Random effects and additional covariates accounting for potential sources of noise (e.g., mean inter-beat interval, time-on-task) may be included if warranted by theoretical considerations and model comparisons (for a similar approach, see [44]). As part of this analysis we will quantify microsaccades frequency and latencies, as well as pupil area trajectory. These findings will be included in the results and, if we find that any of these data features, when considering the period immediately following the cue, differ significantly between conditions we will include these as covariates in the model.

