An important factor, considered in the development of this study protocol, is the potential contribution of arousal in eliciting or promoting awareness, where arousal can take the shape of either phasic (stimulus-specific) or tonic (context-specific) arousal. In basic physiological terms, the role of arousal in psychophysical experiments such as those described here is well understood—specifically, that it enhances neural excitability and, depending on the level, may increase signal-to-noise ratios. Here, the locus coeruleus (LC) system mediates tonic and phasic arousal states affecting overall alertness, while phasic arousal helps fine-tune perception in response to specific stimuli. Studies using pupillometry have directly linked LC activity to changes in sensory processing, reinforcing the idea that arousal plays a major role in perception. All theories should thus expect these physiological processes to be in play, and understood as such the presence of arousal will not directly support one theory over the other. It will be a matter of further interpretation and modelling of the results to specify how arousal aligns with the core tenets of each theory. Here, it is of significance that, according to the active inference framework, arousal in this setting can be read in terms of attentional set and therefore reflects mental active inference, usually involving interoceptive inference [45–51]; this would make the arousal process an indispensable part of the active inference underpinning a change in consciousness. In contrast, for IIT and NREP, arousal would pertain to processes distinct from but interacting in important ways with the core processes posited by NREP and IIT as necessary for consciousness; this difference in outlook on arousal and attention partially explains the differences in the prediction table (shown above) for this experiment; that is, IIT and NREP’s predictions are not the opposite to those of AI-C, but partially overlap, and with weaker confidence. The interpretation of results, in particular differences of arousal between the two conditions, in the light of theoretical commitments will thus help situate the role of arousal and attentional set in diverse theories of consciousness. To help disambiguate the contributions of motor active inference (saccades) and mental active inference (i.e., attention and arousal) to perception, we opted to measure cardiac and pupil responses. Measuring inter-beat interval estimates allows us to adjust for context-specific arousal for a given trial. Pupillometric changes are considered integral to stimulus-bound aspects of active inference [51–53]. Cardiac and pupil data therefore allows us to quantify the contribution of (stimulus-specific and context-specific) attentional set and (saccadic) motor action to changes in perceptual content.

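### Adjusting for cardiac and pupil proxies does not separate the saccade's contribution from arousal, as the Discussion says it does

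*Protocol article*

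**What the plan says.** All references are to the protocol article.

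- **Discussion (arousal paragraph).** Cardiac and pupil responses are measured to help tell saccadic action apart from attention and arousal. Inter-beat interval is said to permit adjustment for tonic arousal on each trial. The paragraph closes with this conclusion: "Cardiac and pupil data therefore allows us to quantify the contribution of (stimulus-specific and context-specific) attentional set and (saccadic) motor action".
- **Current study.** The measures are there "to adjust for any differences in attentional set (e.g., arousal) that could be considered to confound condition-specific differences".
- **Planned analyses and expected outcomes.** Separation is by regression covariates. On the cardiac side: "Random effects and additional covariates accounting for potential sources of noise (e.g., mean inter-beat interval, time-on-task) may be included", subject to theory and model comparison. Pupil and microsaccade features enter the model if, just after the cue, they differ significantly between conditions.
- **Aim, and Experiment A, Main experiment.** Active trials cue a saccade to the target location. Passive trials require central fixation while the array is moved.
- **Operational hypotheses.** NREP has its own arousal route to the same direction of effect: "motor-associated arousal may help to detect stimuli at greater distance from foveation point".

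**The concern.** In the planned model the saccade has no variable of its own. It is present in one condition and absent in the other, so it coincides with the condition indicator. A saccadic contribution can therefore be read only as the condition coefficient that remains once the arousal covariates are in.

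That reading would be sound if the covariates captured arousal without error and the saccade did not disturb them. Trial-level pupil size and heart period are indirect measures of arousal. The article's own processing steps show imperfections: blinks are interpolated, implausible beats are rejected and spline-filled, and the two sites use different ECG leads. Adjusting for an error-prone covariate removes only part of what it stands for.

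What is at stake is the split between motor action and arousal. An effect produced by arousal, which is NREP's explanation, could leave a non-zero adjusted contrast and be reported as the contribution of the saccade.

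**Working it through.** **Inputs from the article.** N = 55, at least 80% power, and a cited study planned "with an effect size of η2p = .13"; the design is within-subject ("This experiment deploys a within-subjects design to contrast differences in the time to reappearance"). Experiment A states 72 trials per condition; the same section also mentions 144 of each type, which does not enter the bias formula.

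**Assumed, because not stated.** Two-sided alpha 0.05; within-condition proxy reliability L from 0.3 to 0.9.

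**1. The plan's own figure.** For a two-level within-subject contrast, dz = √(.13/.87) = 0.387. Exact noncentral-t power for a paired test reaches 80% at N = 55 (80.4%). The stated sample size reproduces.

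**2. Bias with error unrelated to condition.** Let outcome = τ·Active + β·Arousal + noise, and proxy = Arousal + random error. Let Δ be the active-passive difference in arousal. The fitted proxy slope is βL, so the adjusted contrast is

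τ + βΔ − βLΔ = τ + βΔ(1 − L).

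With no motor effect (τ = 0), a share 1 − L of the arousal effect remains.

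**3. Size at the protocol's effect.** Suppose the whole dz of 0.387 is arousal. Holding the standard deviation of the participant differences fixed, the residual dz is 0.387(1 − L), tested at N = 55. The right-hand columns come from a simulation with 55 participants, 72 trials per condition, τ = 0 and 400 runs per setting.

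| Assumed L | Residual dz | Chance of significance | Simulated share left | Simulated rejection |
|---|---|---|---|---|
| 0.9 | 0.039 | 6% | 8% | 6% |
| 0.7 | 0.116 | 14% | 30% | 20% |
| 0.5 | 0.193 | 29% | 50% | 35% |
| 0.3 | 0.271 | 50% | 70% | 50% |

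With a near-perfect proxy (L = 0.999) the simulation rejected in 6% of runs.

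The two rejection columns use slightly different models. The simulation set β = 0.3, Δ = 0.3, a participant SD of 0.75 for Δ and unit trial noise. Its raw effect is 0.3 × 0.3 = 0.09. The SD of participant differences is √[(0.3 × 0.75)² + 2 × 1.09/72] = 0.284, so its raw dz is about 0.32, a little below 0.387. Its unadjusted test rejected in about 61 to 67% of runs. Its adjusted rates are nevertheless mostly higher than the closed form, because adjustment also removes some between-participant variation. The closed form holds that variation fixed.

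**4. The covariate inclusion rule.** When the proxy entered only if its condition difference was significant, it was left out in about 20% of runs, and the whole arousal effect then stayed in the contrast. Overall rejection became 8, 22, 36 and 51% at L = 0.9, 0.7, 0.5 and 0.3.

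**5. If the saccade itself moves the proxy.** Let it shift the proxy by s in active trials. The adjusted contrast becomes τ + β[Δ(1 − L) − Ls]. With s = Δ = 0.3 (assumed), the share left is 1 − 2L: −80, −40, 0 and +40% at the same four values of L. Simulation gave about −85, −38, 0 and +41%. The bias can disappear or change sign.

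**The case against.** **The text is hedged, and the theory verdicts do not use this split.** The sentence introducing the measures says they help to disambiguate. The same paragraph leaves the alignment of arousal with each theory to further interpretation and modelling, and says arousal will not directly support one theory over another. AI-C counts arousal as mental active inference. The section on the current study ties support for AI-C in Experiment A to the active-passive difference, not to an adjusted residual. All of this stands, so a reader who infers that the main contrast or the AI-C verdict is invalid goes further than the documents allow. The hedges do not cover the final sentence, which draws a firm conclusion about what can be quantified.

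**The direction is not fixed.** A reader might infer that the error always favours the motor reading, or that the adjusted contrast is an upper bound on the effect not carried by arousal. Both need error unrelated to condition, and step 5 shows how they fail. The documents do not establish that condition. Over-correction equally defeats the claimed separation, so this objection narrows the point without removing it.

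**The size is assumed.** This is correct: nothing in the article places the reliability of either proxy. Only the existence of a remainder for L below 1 is firm.

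**Measurement-error methods belong in an analysis plan.** This is also fair. The absence of a reliability correction from a condensed article is not the fault raised here. The fault is the positive statement about what these data can quantify.

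**Conclusion.** The concern holds in limited form. The Discussion credits the cardiac and pupil data with a separation that covariate adjustment cannot provide when the saccade coincides with condition and arousal is measured by imperfect proxies.

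Under classical error, 10 to 70% of an arousal effect stays in the adjusted contrast for L between 0.9 and 0.3. If the protocol's design effect were wholly arousal, significance would be found in roughly 6 to 50% of studies, against a nominal 5%. These figures rest on assumed reliabilities, two-sided alpha 0.05, and error unrelated to condition. Without that last assumption the sign of the bias is unknown.

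The sample size and the unadjusted active-passive contrast are unaffected.

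**What to change.** 1. Reword the closing sentence of the arousal paragraph. It should say that cardiac and pupil covariates adjust only partially for arousal, and that the adjusted contrast is neither an estimate of the saccadic contribution nor a bound on it.
2. Report the unadjusted and arousal-adjusted contrasts side by side in every case, whether or not the covariates differ significantly between conditions.
3. Optionally, add a measurement-error sensitivity analysis over a plausible reliability range, estimated from the study's own repeated trials where possible. Present it as descriptive context and not as a pass/fail rule. A rule that the effect must survive every assumed reliability would discard real effects. Correction at assumed reliability r subtracts the arousal effect × L/r. With a true motor effect of 25 ms, an arousal effect of 25 ms, L = 0.6 and r = 0.2 (all illustrative), the result is 50 − 25 × 0.6/0.2 = −25 ms.

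No new data, participants or procedures are needed. The cost is a weaker statement about motor versus arousal contributions and a little more analysis.

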### The adversarial collaboration setting for this study

As mentioned in the Introduction, this study protocol forms part of a consortium project engaged in adversarial collaboration among theories of consciousness, in this particular case NREP and IIT, in addition to AI-C (https://doi.org/10.54224/20646). The results for the basic predictions described above, as well as the results from the other experiments in this adversarial collaboration, will be subject to discussion and comparative interpretation from the consortium, taking into account the overall set of predictions registered in protocols and at the OSF site. Furthermore, an integrative Bayesian analysis according to the scheme set out in [34] may be performed.

### Dissemination plans

The outcomes of this experiment, as with experiments from the two other theories (IIT and NREP) in the adversarial collaboration, will likely be published in one or more stand-alone articles in the first instance, or might be published in the form of a combined paper (i.e., individual experiments within each theory arm may or may not be published together within the same paper). The results of these experiments may be presented in posters and talks at both international and regional conferences.

Following the completion and publication of each set of experiments, additional papers aiming to integrate these findings and discuss their implications for each of the three theories tested in the adversarial collaboration may be published. For example, an integrative analysis along the lines of that proposed by Corcoran and colleagues [34] may be pursued.

Finally, the TWCF Consortium will deliver a public talk or symposium to present and discuss the outcomes of the entire adversarial collaboration.

### Dealing with amendments

In the present experiment and the two other protocols that form part of the INTREPID consortium, amendments will be considered and agreed upon between the teams at both Melbourne and Jena experiment sites, and the three INTREPID consortium theory leads ([name], [name], and [name]). Upon the agreement of any reasonable amendments to the protocol, the amendment will be recorded and timestamped in the existing OSF preregistration documentation (https://osf.io/35rhx).
